### Randomization and masking

Randomization will be computer-generated (using REDCap) with permuted blocks in multiples of two and stratified by gender. The randomization process will be overseen by the study statistician (CP). The treatment allocation will be concealed until the time of randomization. Due to the nature of the intervention, participants and their respective interventionists will be aware of their treatment allocation. The project manager will also be aware of the treatment allocation; all other study staff will be masked. Study participants will enter questionnaire data for the primary study outcome directly into REDCap. Secondary outcomes are objectively measured, and those who will analyze these outcomes will be masked to treatment allocation until study completion. At the baseline visit, the project manager and study participant will be informed of the treatment allocation through REDCap. The project manager will then coordinate the first intervention visit with the appropriate interventionist. If an adverse event occurs, unmasking would be permissible.

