**Methods/design:**

A randomized controlled trial in 50 young adults aged 18 to 35 years with T1D will be used. Eligible subjects will be randomized to the intervention program (Fear Reduction Efficacy Evaluation [FREE]) or attention control group. A one-week run-in phase is planned, with baseline measures of FOH, self-management behavior, A1C, and real-time continuous glucose monitoring recordings (RT-CGM) to calculate GV for both groups. The intervention group will participate in eight weekly individual one-hour sessions using CBT and exposure treatment for specific fears. RT-CGM and a daily FOH diary will be used as feedback cues as part of the FREE program. The attention control group will participate in eight weekly individual one-hour diabetes self-management education (DSME) sessions and wear a RT-CGM device (to measure GV only) over 8 weeks. At completion, FOH will be measured, and RT-CGM recordings will be analyzed to determine differences between the FREE and control groups.

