### Study population and recruitment

Eligible participants will include young adults (18–35 years) with T1D ≥ 1 year, receiving care from an endocrinologist, experiencing FOH (screening questionnaire) [53], who have previously attended a basic diabetes educational program. Exclusion criteria are pregnancy or breastfeeding, receiving psychotherapy for FOH, and having a co-existing chronic illness or receiving medications (excluding insulin) that may influence diabetes self-management or GV.

Participants will be recruited through two medical centers and local diabetes organizations and websites in the midwestern United States. Informed consent will be obtained from each study participant by a trained member of the study team. Those who meet study criteria will be scheduled for an appointment for the start of the one-week run-in period (week 0) and apply a RT-CGM device with instructions on its care. Participants will be randomly assigned to the FREE intervention or attention control group. During the study period, participants will continue to receive their usual diabetes care, and their health care providers will continue to care for their diabetes as they normally would.

Participants will be assigned a unique code number. A master list that links the subject identity to the data will be kept by the principal investigator (PI) and stored in a locked office separately from the data. All data will be stored and analyzed by code number. The coded data will be entered into a password-protected computer with a secure server for analysis. Paper copy data will be stored in a locked office.

Criteria for discontinuing participation for a given trial participant include: a) participant request or b) determination by the psychologist/interventionist that continuation of the study would not be appropriate due to confounding psychological issues that become evident during the study. If this occurs, a list of counseling resources will be provided.

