### Measures

Data will be collected (1) at the beginning of a one-week run-in period (week 0); (2) at week 4; (3) upon completion of the intervention (week 8); and (4) post-program (week 12). FOH, self-management, and A1C will be measured, and RT-CGM recordings will be analyzed to determine within-group and between-group differences (Fig. 3).

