### Statistical analysis

The statistical estimation method for this study is a mixed-effects model with repeated measures (SPSS).

Aim 1: Feasibility will be evaluated by assessing recruitment, retention, and participant evaluation. Records will be kept of the number of recruited, screened, eligible, and consented subjects. Retention will be evaluated by weekly attendance (percentage session attendance, program completion rates). Acceptability will be determined through participant evaluation (written evaluation and interview at program completion and a convened advisory group of previous participants). As part of feasibility, we will also track the number of RT-CGM sensor failures, placement sites, time to failure, and adverse sensor site problems.

Aim 2: We will evaluate the effects of within-group and between-group differences from baseline (week 0) to program completion (week 8) and post program (week 12) on the outcomes FOH, self-management, glycemic control, and GV, using an intent-to-treat approach. To address sex as a biologic variable, sex differences in primary and secondary outcomes will be explored. Diabetes duration and depressive mood will also be statistically controlled.

Hypothesis 1: FOH will be reduced. Within-group and between-group differences in HFS worry score from baseline to study completion and post program will be compared using a mixed-effects model.

Hypothesis 2a: Diabetes self-management will be improved. Within- and between-group differences in the Diabetes Self-Management Scale score from baseline to study completion and post-program will be compared using a mixed-effects model.

Hypothesis 2b: Glycemic control. Within- and between-group differences in A1C from baseline to study completion and post-program will be compared using a mixed-effects model.

Hypothesis 2c: GV will decrease. GV will be determined through GlucSD, CONGA, CV%, and IQR, as well as daily time spent in hypo- or hyperglycemia. Within- and between-group differences will be calculated from daily RT-CGM recordings using a mixed-effects model.

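### Allocation is disclosed at the baseline (week 0) visit, so on the natural reading the run-in CGM week that supplies baseline glycemic variability is recorded after participants know their arm

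*Protocol article*

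**What the plan says.** All references are to the protocol article.

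- **Randomization and masking** sets the time of disclosure: "At the baseline visit, the project manager and study participant will be informed of the treatment allocation through REDCap". The next step is "The project manager will then coordinate the first intervention visit with the appropriate interventionist". The section also says that participants are not masked.
- **Study population and recruitment** has those who meet the criteria "scheduled for an appointment for the start of the one-week run-in period (week 0) and apply a RT-CGM device". The following sentence is "Participants will be randomly assigned to the FREE intervention or attention control group", with no time attached.
- **Measures**: "Data will be collected (1) at the beginning of a one-week run-in period (week 0", with later collections at weeks 4, 8 and 12.
- **Statistical analysis**, Aim 2, evaluates differences "from baseline (week 0) to program completion (week 8) and post program (week 12".
- **Abstract, Methods/design**: "A one-week run-in phase is planned, with baseline measures of FOH". The same sentence adds self-management, A1C and the CGM recordings from which GV is calculated.
- **Table 3** lists GV at weeks 0 to 8. **Interventions** says that both arms continue with an unblinded device through the 8 weeks of sessions.

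**The concern.** A baseline is a fair reference for a randomised comparison when it cannot depend on the arm, and that is secured by recording it before the participant learns the allocation. Here the order appears to be reversed for the CGM week. GV responds to what people eat, how often they snack and how they adjust insulin, and the article's Background says that fear alters these behaviours. A participant who has just learned that fear-focused therapy, or an education course, is about to start may behave differently in that week while glucose readings are visible. Allocation concealment does not help, because it ends at randomisation. Masked analysis of the sensor data does not help either, because the participant's behaviour, not the reading of the data, is what could change.

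At stake is the GV part of the secondary hypothesis, together with any GV effect size carried forward to plan the larger study.

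**Working it through.** The plan gives no figure to reproduce. The check is of the order of events, followed by how a shift in baseline would pass into the contrast.

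**Order of events**

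1. Baseline is week 0 (Statistical analysis).
2. Week-0 data are collected "at the beginning of a one-week run-in period (week 0" (Measures).
3. The week-0 appointment opens the run-in, and the CGM device is applied then (Study population and recruitment).
4. The arm is disclosed at the baseline visit (Randomization and masking).
5. From 1 to 4, disclosure falls at the visit that opens the run-in. No other visit is called baseline, and no text shown puts randomisation or disclosure at the end of the run-in.
6. The first session is booked after disclosure, so it is a separate, later visit. The run-in week lies between the two.
7. GV is recorded only in weeks 0 to 8 (Table 3), so the run-in week is the only GV record before the sessions. On this order, all 7 of its days follow disclosure.

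The run-in display is not described directly. That participants *continue* with an unblinded device suggests the same display in the run-in.

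**How a shift would pass through**

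Let d be the between-arm difference in baseline GV caused by knowing the allocation, in SD units. Let rho be the correlation between baseline and follow-up GV, with equal SDs at both times.

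- Change from baseline: contrast = effect of assignment − d, so the bias has size d.
- Baseline as covariate: contrast = effect of assignment − rho × d, so the bias has size rho × d.

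The document gives neither d nor rho. The values below are assumptions chosen only to show the scale.

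| d (SD) | Bias, change score | Bias, covariate, rho = 0.3 | rho = 0.5 | rho = 0.7 |
|---|---|---|---|---|
| 0.1 | 0.10 | 0.03 | 0.05 | 0.07 |
| 0.2 | 0.20 | 0.06 | 0.10 | 0.14 |
| 0.3 | 0.30 | 0.09 | 0.15 | 0.21 |

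Covariate adjustment shrinks the bias but does not remove it. The sign is open. Lower baseline GV in the FREE arm would understate its benefit, and lower baseline GV in the control arm would overstate it.

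**The case against.** The strongest reply is that the timing is inferred. The baseline visit is named once and never defined. The abstract treats the whole run-in as the baseline phase, so disclosure at a visit closing that week is not excluded, and booking the first session afterwards fits either order. The SPIRIT figure, which could settle it, is not shown in the text available. This stands as a limit on certainty. It does not remove the point, because the article's own definition of baseline points to the start of the run-in. If the figure shows the other order, the masking section needs correcting to match.

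It can also be said that both arms get eight weekly individual one-hour sessions, homework and a CGM device, and that no session takes place in the run-in. Only anticipation could act. That is true, and it is a reason to expect a modest effect rather than none.

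A reader might infer three stronger things, none of which the document supports:

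- **Bias in the primary fear score.** Questionnaires are taken at the start of week 0, and the article does not say whether they come before or after disclosure within that visit. An article commonly leaves this to the full protocol. Silence does not show that the fear score is collected after disclosure.
- **A bias expressed as a share of the planned effect size of 0.72.** That figure was derived from fear-of-hypoglycemia levels. No effect size is planned for GV, so the ratio would have no meaning for the outcome at issue.
- **Run-in losses as a flaw.** The run-in is described as a measurement period, not a screen for likely drop-outs, and 20% attrition is already planned for. Placing it before randomisation in order to filter participants would be a preference.

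**Conclusion.** The point holds for baseline GV. As the article reads, unmasked participants know their arm before the only pre-session GV week is recorded, and the GV contrasts from baseline are open to a bias that analysis cannot fully remove. This rests on three assumptions: that the baseline visit is the week-0 visit, that the run-in device shows its readings, and that knowing the arm changes behaviour. The first is the natural reading, the second is suggested by the text, and the third is plausible but unmeasured. The size and direction cannot be derived from the document, and the SD values in the table are illustrations, not estimates. A1C is a fingerstick reflecting 2 to 3 months of glucose, so it is little affected. Severity is moderate: a secondary outcome in a pilot, with a simple remedy.

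**What to change.** In Study population and recruitment, Randomization and masking, and Measures, state one order:

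1. Week-0 questionnaires and A1C.
2. The full 7-day run-in CGM recording.
3. REDCap randomisation and disclosure of the arm, made when session 1 is booked.

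If the SPIRIT figure already shows this order, correct the sentence on disclosure in Randomization and masking to agree with it.

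Flag participants enrolled under the present order. Report the GV analysis with and without them, or by order, as a sensitivity check. In a trial of this size the reduced analysis may be imprecise, so it should be read as a check and not as a replacement.

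Cost: a small amendment with no extra visit or staff. Session 1 may be scheduled slightly later. Baseline timing will be mixed across the cohort, because the first participant was enrolled in January 2019. Anyone who leaves during the run-in would then be lost before randomisation, so the Aim 1 recruitment and retention records should still count them.

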### Interventions

Participants randomized to the FREE intervention group will: (1) attend eight individual weekly one-hour sessions based on principles of CBT and exposure treatment (Table 1). Treatment will target incorrect beliefs about hypoglycemia, hypervigilance to symptoms, fear of symptoms, and maladaptive behavioral responses in response to glucose levels. Participants will create a fear and avoidance hierarchy and be taught to begin approaching previously feared situations (e.g., spending time alone, reducing snacking, allowing glucose readings to reach lower safe levels, etc.) to experience habituation and the resulting decrease in anxiety. Weekly homework will be assigned to reinforce the content. (2) FREE intervention subjects will continue to wear an unblinded RT-CGM for the 8 weeks and (3) complete a daily FOH diary. RT-CGM readings and daily diaries will serve as feedback cues for glucose and FOH levels as part of the FREE program.

**Table 1 Tab1:** Elements of the FREE program

Elements of the FREE Program	
Hypoglycemia and its causes	Week 1
Fear as a normal human emotion	
Effect of fear on health and health behaviors	
Safety and avoidance behaviors	
Blood glucose cues	Week 2
Introduction to CBT	
Cognitive restructuring, safety behaviors	Week 3
Introduction to progressive relaxation	
Exposure therapy: develop fear hierarchy	Week 4
Coping strategies	
Exposure practice, coping, relaxation, and cognitive restructuring	Weeks 5–7
Review techniques learned, develop a plan to maintain gains	Week 8

Participants randomized to attention control will attend eight weekly individual one-hour sessions on diabetes self-management education (Table 2). Topics follow the American Diabetes Association DSME standards [54] and will be led by a certified diabetes educator (CDE). Weekly homework will be assigned. Participants will continue to wear an unblinded RT-CGM for the 8-week session (for GV measurement *only*) but will *not* keep a diary.

**Table 2 Tab2:** Elements of the attention control (DSME) program

Elements of the attention control (DSME) program	
Living with type 1 diabetes	Week 1
Using insulin safely: blood glucose monitoring	Week 2
Healthy eating: incorporating nutritional management into lifestyle	Week 3
Healthy eating: carbohydrate counting	Week 4
Being active: incorporating physical activity into lifestyle	Week 5
Healthy sleep	Week 6
Diabetes in the workplace	Week 7
Preventing complications Review and wrap-Up	Week 8

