Over the past three decades, newer technologies have been designed to help patients with diabetes manage their treatment regimens, including continuous glucose monitoring (CGM) systems, insulin pumps, sensor-augmented pump therapy with insulin suspend features, and insulin bolus calculators. While these have improved glucose control (i.e., A1C), improved A1C has not consistently translated into reduced FOH [28–34]. Diabetes education programs typically discuss FOH but have limited strategies to manage it [4]. Glucose management and blood glucose awareness training have had variable effects on FOH [4, 35–43]. Outcomes demonstrated that, as glucose levels lower, worry levels do not consistently decrease [43]. We hypothesize that the lack of consistent and sustainable reductions in FOH has occurred because the focus of these programs has been on glycemic control, not FOH.

GV has been associated with more frequent episodes of hypoglycemia [44] and fluctuations between glucose extremes (i.e., hypo- to hyperglycemic), which may occur with overtreatment of a hypoglycemic episode. Evidence supports the role that GV plays in generation of oxidative stress [45], endothelial dysfunction [46], and diabetes complications in T1D [47]. GV has also been associated with increased risk for cardiovascular events [63]. Though A1C provides a biomarker for average blood glucose over a 2- to 3-month period, it does not capture daily blood glucose fluctuations (Fig. 1). Individuals may have an optimal A1C yet high GV [48]. GV is influenced by self-management behavior [49] and amenable to change with appropriate intervention.

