**Fig. 1 Fig1:**
[figure not shown]
Glycemic variability

The proposed study will pilot test a cognitive behavioral therapy (CBT)-based program to decrease FOH and examine its association with GV. Heightened fear develops from memories of previous negative hypoglycemic events that create a conditioned negative response to future fear triggers [11, 50]. The conditioned fear response is reframed through cognitive restructuring of negative thoughts, regulation of emotions (FOH), and changing maladaptive behaviors (self-management behavior). Exposure therapy will be used to reduce FOH that is out of proportion to the threat through habituation to previously fearful situations (Fig. 2) [51]. Real-time continuous glucose monitor (RT-CGM) readings and fear diary review will be feedback cues to reinforce learning. The goal is not to replace standard diabetes therapy, but improve diabetes self-management [52] through reducing fear. The CBT intervention will be compared to usual diabetes education currently in place to address self-management behavior.

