## Discussion

This study protocol directly focuses on FOH reduction. This study will generate information for a larger clinical trial to test the effectiveness of the FREE intervention compared to diabetes management education to reduce FOH, improve self-management behavior, and improve glycemic control and GV. If effective, this intervention will serve as an important adjunct to diabetes care in young adults with T1D, reduce the development of diabetes complications, and improve quality of life.

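### Within-group A1C change would include the effect of starting the study's visible RT-CGM, so program-effect claims should rest on the between-group difference and the Background should name the comparator accurately

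*Protocol article*

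**What the plan says.** All references are to the protocol article.

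- **Device start.** Under Study population and recruitment, every eligible participant attends for the "start of the one-week run-in period (week 0) and apply a RT-CGM device with instructions on its care".
- **FREE arm.** Under Interventions, "FREE intervention subjects will continue to wear an unblinded RT-CGM for the 8 weeks", and the device has a program role: "RT-CGM readings and daily diaries will serve as feedback cues for glucose and FOH levels as part of the FREE program".
- **Control arm.** The same section gives eight individual weekly DSME sessions and adds "Participants will continue to wear an unblinded RT-CGM for the 8-week session (for GV measurement *only*) but will *not* keep a diary". The abstract's Methods/design paragraph agrees: control participants "wear a RT-CGM device (to measure GV only) over 8 weeks".
- **Name of the comparator.** The Background, after Fig. 1, says "The CBT intervention will be compared to usual diabetes education currently in place to address self-management behavior". The aims and both hypotheses instead call this arm an attention control.
- **What CGM does.** The Background lists CGM with pumps, suspend features and bolus calculators, and says of the group: "While these have improved glucose control (i.e., A1C), improved A1C has not consistently translated into reduced FOH". It also describes A1C as reflecting average glucose over 2 to 3 months.
- **Planned contrasts.** Sample size determination names within-group as well as between-group differences, and effect sizes for a larger study, as goals. Statistical analysis repeats both contrasts for Aim 2 and for each hypothesis, including A1C under Hypothesis 2b.

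**The concern.** A participant who can see a real-time glucose reading can act on it, whatever the study team collects it for. The control arm therefore receives more than education, and the Background's description of the comparator does not match what is delivered.

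The consequence falls mainly on one planned analysis. Aim 2 asks for the impact of the FREE program, and within-group change is one of the two contrasts meant to answer it. If A1C falls from week 0 to week 8 within the FREE arm, part of the fall may come from starting the study device. The same holds within the control arm. A within-group effect size passed to the larger trial would carry that component with it.

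**Working it through.** The plan gives no figure for a CGM effect, so there is none to reproduce. Its one design figure, the effect size of 0.72, is for fear of hypoglycemia, and this point does not rest on it.

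**1. Device exposure (Study population and recruitment, Interventions, Table 3).** It is the same in both arms:
- run-in: 1 of 1 week
- weeks 1 to 8: 8 of 8 weeks, so 1 + 8 = 9 weeks on the device by week 8
- weeks 9 to 12: 0 of 4 weeks scheduled. Usual care continues, so a participant could still be wearing a device of their own.

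**2. What each A1C covers.** Take the Background's 2 to 3 months as about 8.7 to 13 weeks and, as a simplification, weight all weeks equally.
- Week 0, at the start of run-in: 0% of the window is on the study device.
- Week 8: with an 8.7-week window, all of it (9 weeks exceeds 8.7); with a 13-week window, 9/13 = 69%.
- Week 12: with an 8.7-week window, (8.7 − 4)/8.7 = 54%; with a 13-week window, 9/13 = 69%.

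The week-0 value is off the study device, and the later values are largely on it.

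**3. What each contrast estimates.** For A1C change from week 0 to week 8, let P_F and P_C be the effects of the FREE and DSME programs, d the effect of starting the visible device, and t any other change over time. Assume that these add.
- Within FREE: P_F + d + t
- Within control: P_C + d + t
- Between groups: (P_F + d + t) − (P_C + d + t) = P_F − P_C

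Each within-group change differs from its program effect by d + t. The between-group difference contains neither. If FREE participants gain more from the device because the program uses its readings as feedback, that extra gain belongs to P_F and is part of the package under test.

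**4. Size of d.** The documents do not give it. If a proportion u of participants already uses CGM and gains nothing further (an assumption), the average is d = (1 − u) × d0, where d0 is the effect in a new user. Prior use is neither reported nor an exclusion, so u may lie anywhere from 0 to 1, and the distortion anywhere from d0 to none.

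**5. Glycemic variability.** Table 3 measures it in weeks 0 to 8 only. Every value, including the baseline, is recorded on the same type of visible device, and there is no week-12 value. The before-and-after mismatch in step 2 does not arise.

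**The case against.** The strongest reply is that the design is balanced on purpose. Both arms have the same device over the same period, partly as a retention measure, and this separates CBT with feedback from mere access to a monitor. The primary hypothesis is a between-group comparison of fear of hypoglycemia. That reply stands, and it excludes several stronger readings that a reader might infer:

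- **That the device biases the randomized comparison or undermines the primary outcome.** It is common to both arms. The Background gives no CGM-specific effect and says that fear was not consistently reduced by these technologies.
- **That the measurement-only phrase is false and should go.** Set beside the sentence on feedback cues in the FREE arm, it plausibly means that the readings play no part in the DSME program. The same sentence calls the device unblinded, so nothing is hidden. Deleting the phrase would remove the only hint of that contrast.
- **That the hypotheses and the Discussion also misname the comparator.** The hypotheses say attention control. The Discussion describes a future study, "to test the effectiveness of the FREE intervention compared to diabetes management education to reduce FOH, improve self-management behavior, and improve glycemic control and GV", and does not call that education usual.
- **That effect sizes handed to the larger trial will be wrong because its control arm will lack RT-CGM.** Nothing in the article says that it will.

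It can also be said that mixed causes limit any before-and-after change, and that the article never credits such a change to the program alone. This is largely fair and is why the severity is low. It does not dispose of the point: within-group contrasts are planned under an aim about program impact, and the article itself counts CGM among technologies that improve A1C.

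**Conclusion.** The concern holds in a limited form, at low severity. The comparator under test is eight individual DSME sessions with visible RT-CGM, and one Background sentence describes it loosely. The between-group results remain valid for that comparison. A within-group week 0 to week 8 A1C change cannot be read as a program effect, because it contains the unknown d defined above along with any other change over time.

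This rests on three things: that visible readings can influence behavior, which the article implies by using them as feedback in the FREE arm; that at least some participants are not already using CGM, which the article does not state; and that the device effect is common to the arms apart from what the FREE program adds. If every participant already used CGM, the A1C part of the point would largely disappear and only the wording of the comparator would remain.

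**What to change.** - **Statistical analysis.** Base the conclusion for Hypothesis 2b on the between-group difference in change, adjusted for the week-0 value. For consistency, do the same for 2a and 2c. Take any effect sizes for the larger trial from these contrasts. Report within-group changes as descriptive only.
- **Background, after Fig. 1.** Name the comparator as attention-control DSME plus unblinded RT-CGM.
- **Abstract (Methods/design) and Interventions.** Keep the measurement-only phrase, and add that it means the readings are not used in the control program, if that is the intent.
- **Hypotheses and Discussion.** No correction is needed.

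The cost is a few sentences, with no change to treatment, visits or data. The price is a narrower claim: the trial would speak to FREE against DSME among participants who all wear RT-CGM, and would make no program-effect statement from change within one arm.
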